## Introduction

 Over 530 000 people die each year in the UK^1^ and this number is increasing.^2^ Many of these deaths are associated with people living with multiple morbidities and complex end-of-life care issues.^3^ The National Health Service (NHS) should provide high-quality, safe, person-centred end-of-life care consistent with their wishes.^4^ Most people wish to die at home.^5 6^ Additionally, hospital was the least preferred place of death for patients receiving palliative care in three countries.^6^ However, more than half of UK people currently die in hospital^2^ and many experience unplanned hospital admissions, including emergency department visits and unwanted and futile aggressive treatment.^27^,^9^ Failure to address these critical issues undermines the realisation of benchmarks that define a good death, as perceived by individuals, their families and healthcare providers alike.^10^,^12^

Advance care planning (ACP) is a voluntary process that supports adults in considering and sharing their values, goals and preferences regarding future care, including location of death so that if they lose mental capacity to make informed decisions for themselves, health professionals and their families can provide care consistent with their wishes.^13^ In the UK, ACP is endorsed in national policy.^14^ Despite scepticism of its value,^15^,^17^ an intrinsic logic of ACP underpins its use in practice and justifies continued research. Potential ACP benefits include providing important opportunities for discussion of diagnosis and prognosis so care and treatment are aligned with individuals’ preferences, improving symptom discussions and treatment adherence and reducing misunderstandings and conflict between medical staff and families.^18^ ACP may also lead to fewer interventions of limited or futile clinical value, earlier access to palliative care, reduced inappropriate emergency hospital admissions, fewer hospital deaths and increased rates of hospice admission or appropriate care at home.^19^,^21^ ACP is thought to help families prepare for the death of a loved one, resolve family conflict and help with bereavement.^22^ Although primarily concerned with improving the appropriateness and quality of care, ACP may contribute to controlling important health spending and making more appropriate and considered use of scarce resources in end-of-life.^18 23^

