The study will describe how EPaCCS are used, specifically who creates EPaCCS records and what information they encompass regarding individuals’ preferences for end-of-life care. The study will describe data fields across each of the three datasets and evaluate their completeness. Additionally, a descriptive analysis of the three EPaCCS datasets will be undertaken to describe the creation and content of the records across the three regions. These specific regions were chosen for being large metropolitan areas with varied levels of material deprivation and a high concentration of ethnic minority groups. This analysis will focus on the elements of ACP used to support decision-making at the end of life, which include documentation of the ceiling of treatment, resuscitation status, preferred place of care and preferred place of death. The study will also explore if changes are made to decision-making over time for each of these elements. As the three EPaCCS in the study contain data from different periods in time, we will take into account the different timescales during the analyses. The uptake of EPaCCS will be evaluated by describing the number of records created across different time periods and locations. The study will also investigate the setting of the initial record creation (hospital care, primary care, community care). Furthermore, the study will describe the clinical characteristics of patients such as their diagnosis, performance status, capacity for decision-making, living arrangements and expected prognosis. The study will also describe their socio-demographic characteristics with a particular emphasis on social determinants of health such as age, gender, socioeconomic position and ethnicity. The socioeconomic position will be defined using the Index of Multiple Deprivation (IMD), a standard scoring system based on a range of economic, social and housing data, creating a single deprivation score for each small area of the country. Using methodology previously employed in studies by the research team,^43 44^ an IMD score will be created for each patient based on their postcode which will reflect the deprivation data for the Lower-layer Super Output Area (LSOA) within which the postcode falls. Moreover, the study will investigate across sites the association between social determinants of health and the completion of each of the four previously mentioned ACP elements. Table 2 shows the mapping of the study objectives to data sources and eligibility criteria. Exclusion criteria for all data sources are participants who have chosen National Data Opt-Out and those who have withdrawn consent.

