
**Table 2 T2:** Mapping study objectives to data sources and eligibility to be included in analyses

Objectives		Data sources and eligibility
Work package 1		
1A	To describe and categorise the data fields and completeness of data contained within each EPaCCS register.	Anonymised EPaCCS data from London (CMC, n=140 000), Leeds (n=15 500) and Bradford (n=17 000)
1B	To describe the creation and content of EPaCCS records and elements relating to end-of-life decision-making preferences and ACP (ceiling of treatment, preferred place of care, and death and resuscitation status) in different regions across England.	
1C	To describe the socio-demographic and clinical characteristics of individuals who have created EPaCCS records in different regions across England.	
1D	To estimate associations between social determinants of health (socioeconomic position, ethnicity, age, and gender) and the completion of elements of ACP within EPaCCS.	
1E	To estimate associations between social determinants of health (socioeconomic position, ethnicity, age, and gender) and the creation of EPaCCS.	WSIC-CMC dataset of North West London deceased patients with/without EPaCCSLeeds decedent dataset 2021–2023 of deceased patients with/without EPaCCS
Work package 2		
2A	To explore the effect of EPaCCS on place of death and hospital use in the last 90 days of life.	WSIC-CMC dataset of North West London deceased patients with/without EPaCCSLeeds decedent dataset 2021–2023 of deceased patients with/without EPaCCS
2B	To explore the effect of an EPaCCS record on healthcare costs in the last 90 days of life.	WSIC-CMC dataset of North West London deceased patients with/without EPaCCS

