### Analysis

The data from each of the three distinct EPaCCS will be analysed separately. Individual patient-level EPaCCS data will be accessed and cleaned for each of the three systems. The study will categorise the data into social determinants of health (age, gender, ethnicity, social deprivation), clinical characteristics and elements relating to ACP. The social determinants of health have been identified from existing literature for being associated with poor health experiences and outcomes. The study will assess the completeness of variables in the data, examining patterns of missing data at the individual level and identifying any outlier records. Based on the characteristics of missing data, the study will adopt an appropriate approach to treating missing data for statistical analysis. Several methods will be considered that are appropriate for missing at random and not missing at random data. Though, it is assumed that the missing mechanism will be missing not at random. However, no robust methods of imputing missingness in the independent variables with a missing not at random mechanism have been identified. If imputation was carried out, a sensitivity analysis will be conducted to compare parameter estimates with/without imputation. Missing values for key outcomes will be imputed using gender, age, comorbidity, cause of death, IMD and/or study area.^45^ For each ACP element, documented decisions will be categorised to create an outcome (binary or ordinal) variable for inclusion in logistic regression modelling of the relationship between each of these outcomes, as distinct analyses, and social determinants of health, adjusting for major confounding variables and consideration of random effects/fixed effects (eg, comorbidity). Confounders will be selected using expert knowledge, existing literature, and the completeness and availability of the data. Using the London and Leeds datasets, a dichotomised binary outcome of whether or not a patient has an EPaCCS record will be created for logistic regression, modelling the association between the creation of EPaCCS records and social determinants of health. The study will identify both similarities and differences between the creation, use and content of EPaCCS records in the three EPaCCS cohorts. Mindful of the reported challenges associated with the interoperability of EPaCCS data,^46^ the comparison of datasets will be cautiously approached. We will examine the impact of the significant increase in EPaCCS records in London,^47^ and potentially the two other cities, following the outbreak of COVID-19 in March 2020 in terms of the documentation and completeness of ACP elements within the EPaCCS records. We will carry out a secondary analysis (sensitivity analysis) excluding individuals whose records were created during the COVID-19 pandemic after examining the data and the trend in the creation of EPaCCS records.

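### The work package 1 rule to impute key outcomes does not exempt the ACP elements, although for objective 1D a blank ACP field is itself the outcome (not completed)

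*Protocol article*

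**What the plan says.** Objective 1D is worded in terms of completion: in Table 2 the outcome is "and the completion of elements of ACP within EPaCCS", and the work package 1 text plans to study "the association between social determinants of health and the completion of each of the four previously mentioned ACP elements". The four elements are ceiling of treatment, resuscitation status, preferred place of care and preferred place of death.

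The Analysis section then sets this rule: "Missing values for key outcomes will be imputed", from some or all of age, gender, deprivation, comorbidity, cause of death and study area. The sentence carries no condition. *Key outcomes* is not defined, and ethnicity is not among the predictors. The next sentence builds the 1D outcomes: "For each ACP element, documented decisions will be categorised to create an outcome (binary or ordinal) variable". It does not say what happens to a record with no documented decision.

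The other regression outcome in work package 1, for objective 1E, is "a dichotomised binary outcome of whether or not a patient has an EPaCCS record will be created for logistic regression".

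Three further statements bear on the point. The same section says that "it is assumed that the missing mechanism will be missing not at random". It promises a comparison of estimates with and without imputation if imputation is done. For work package 2, the Missing data considerations section drops patients with unknown place of death from the multivariable analysis and does not impute them.

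**The concern.** For a completion outcome, an empty field is the event of interest. Imputing it as if it were an unobserved value turns people without a documented element into people with one. For an outcome built from the decision itself, imputation supplies a preference for someone who may never have been asked or who declined. The Introduction says that "Advance care planning (ACP) is a voluntary process", so having no recorded preference is a legitimate state and need not be a data fault.

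Objective 1D is a central equity analysis of work package 1. The likely direction of error is towards no difference between groups, so a real inequality could be understated.

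**Working it through.** **Which outcomes can the rule reach?** The protocol does not say, so this step is inference.
- Objective 1E: absence of a record is one of the two outcome values, so there is nothing to impute.
- Place of death (work package 2 primary outcome): the Missing data considerations section excludes missing values, so reading the rule this way would contradict that section.
- Time in hospital (work package 2 secondary outcome): not ruled out by that section, but the sentence stands in the work package 1 analysis.
- ACP elements (objective 1D): they belong to this work package, can be blank, and are constructed in the very next sentence.

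The ACP elements are therefore the most natural target.

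**Inputs.** The protocol gives no completion rates, so there is no stated figure to reproduce. All rates below are assumptions.

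**Case 1: completion outcome, raw field filled before the flag is derived.** Let c be true completion and f the share of blanks filled, equal in both groups. Completion becomes c + f(1 − c), and the gap becomes (1 − f) times the true gap.
- 70% v 55%, f = 0: OR = (0.55/0.45)/(0.70/0.30) = 0.52; gap 15 points.
- f = 0.5: 85% v 77.5%; OR = (0.775/0.225)/(0.85/0.15) = 0.61; gap 7.5 points.
- f = 1: 100% v 100%; gap 0, OR not estimable.

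Other assumed rates, f = 0 then f = 0.5:
- 90% v 80%: OR (0.80/0.20)/(0.90/0.10) = 0.44, then (0.90/0.10)/(0.95/0.05) = 0.47.
- 80% v 65%: OR (0.65/0.35)/(0.80/0.20) = 0.46, then (0.825/0.175)/(0.90/0.10) = 0.52.
- 60% v 40%: OR (0.40/0.60)/(0.60/0.40) = 0.44, then (0.70/0.30)/(0.80/0.20) = 0.58.

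The percentage-point gap halves each time, while the odds ratio moves less.

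**Case 2: completion flag derived first from the raw field.** Every record is 0 or 1. There is no missing value, the rule has nothing to fill, and no harm follows.

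**Case 3: decision-content outcome, blanks imputed without ethnicity.** Assume the decision is made by 70% v 55% in two ethnic groups (OR 0.52) and that the second group is 20% or 40% of records. Blanks are filled at the pooled documented rate. Worked example, completion 80% v 65%, second group 20%:
- pooled rate = (0.8×0.80×0.70 + 0.2×0.65×0.55)/(0.8×0.80 + 0.2×0.65) = 0.5195/0.77 = 0.675
- group 1 = 0.80×0.70 + 0.20×0.675 = 0.695
- group 2 = 0.65×0.55 + 0.35×0.675 = 0.594
- OR = (0.594/0.406)/(0.695/0.305) = 0.64

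Odds ratios after imputation (20% share, then 40% share):
- completion 90% v 80%: 0.59, 0.58
- completion 80% v 65%: 0.64, 0.63
- completion 60% v 40%: 0.75, 0.74

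This case treats ethnicity as unrelated to the listed predictors. Any correlation, for example with deprivation, would lessen the dilution.

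**The case against.** A reader might infer that the protocol orders blank ACP fields to be imputed and so erases the inequality however the outcome is coded. The text does not support that. It never names the ACP fields as the key outcomes, and a flag derived first is untouched by the rule. Decision coding gives dilution, not erasure. Elsewhere the plan treats blanks as information: objective 1A measures completeness, and the COVID-19 analysis looks at completeness of the ACP elements.

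The surrounding text also softens the rule. The approach is to be chosen after missingness has been characterised, and estimates with and without imputation will be compared if imputation is done. Nor does the protocol show that every blank means not completed. The registers differ, and it warns of interoperability problems. Finally, this is a condensed article and a full statistical analysis plan is promised.

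Much of this stands, and it limits the size of the claim. It does not remove the point. The comparison could expose the effect, but the text does not say which analysis is primary, and the comparison does not settle what a blank means. Building the outcome from documented decisions leaves undocumented ones without a stated category, so they fall to the imputation rule by default. The complaint is about a rule that is stated, not about detail left to a later document.

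**Conclusion.** The point holds in limited form. The imputation rule and the 1D completion outcome are not reconciled, and the rule's natural reach, by inference, includes blank ACP fields.

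The consequence depends on the order of operations and the coding. Filling raw fields before deriving completion shrinks the gap by the share filled, given equal shares in both groups: OR 0.52 to 0.61 with half filled, not estimable with all filled, for assumed completion of 70% v 55%. Deriving completion first does no harm. Imputing decision content without ethnicity, which is a 1D exposure, moves an assumed OR of 0.52 to about 0.58–0.75 and assigns preferences where none are recorded. Under both harmful routes the bias is towards no difference. Total loss of the contrast arises only when every blank is filled before completion is derived. It should not be presented as what the protocol prescribes.

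**What to change.** - State that for objective 1D completion is derived from the raw field, with a blank coded as not completed and never imputed.
- Add a sensitivity check for periods or registers in which the field was not held or was lost in extraction, since there a blank does not show non-completion.
- Analyse decision content as a separate outcome among records where the element is documented, and report the documented share by group beside it.
- Define *key outcomes*, limit the imputation sentence to variables other than the ACP elements, and reconcile it with the exclusion rule for place of death in Missing data considerations.

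The cost is a few sentences in the Analysis section, carried into the statistical analysis plan. No new data are needed.

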The PREPARE study therefore aims to (a) describe the characteristics of people who receive EPaCCS to support decision-making at the end of life and to estimate the association between social determinants of health and the content of ACP contained within EPaCCS and (b) explore EPaCCS effect on healthcare outcomes, use and costs. Based on our findings, we will synthesise recommendations on the use of EPaCCS to support end-of-life care for people living with life-limiting illnesses and their families.

The study objectives are the following:

1A. To describe and categorise the data fields and completeness of data contained within each EPaCCS register.

1B. To describe the creation and content of EPaCCS records and elements relating to end-of-life decision-making preferences and ACP (ceiling of treatment, preferred place of care, and death and resuscitation status) in different regions across England.1C. To describe the socio-demographic and clinical characteristics of individuals who have created EPaCCS records in different regions across England.1D. To estimate associations between social determinants of health (socioeconomic position, ethnicity, age and gender) and the completion of elements of ACP within EPaCCS.1E. To estimate associations between social determinants of health (socioeconomic position, ethnicity, age and gender) and the creation of EPaCCS.2A. To explore the effect of EPaCCS on place of death and hospital use in the last 90 days of life.2B. To explore the effect of an EPaCCS record on healthcare costs in the last 90 days of life.

This HRA-approved protocol (V.1.1; January 2025) outlines in detail the motivation for this study, data sources, analysis plan, public and patient involvement, and ethical considerations.

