### Missing data considerations

Individual-level missing data of the primary outcome variable (place of death) will be excluded from the multivariable analysis. However, in handling missing data related to covariates, those with incomplete data will be identified for a thorough characterisation of the missingness. Depending on the type of data and the level and mechanism of missingness, individual patients without matching covariate data may be excluded from the multivariable modelling. In doing so, we would also be mindful that by excluding such patients, modelling could be subject to biases, for example, due to under-reporting. Hence, we may consider imputing missing data, with sensitivity analysis to determine the effectiveness of imputation on the model outputs.

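### The predictor list for imputing missing outcomes omits ethnicity and makes deprivation optional, which attenuates their adjusted associations wherever documented advance care planning decisions are imputed

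*Protocol article*

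**What the plan says.** Objective 1D, in the Introduction, is: "To estimate associations between social determinants of health (socioeconomic position, ethnicity, age and gender) and the completion of elements of ACP within EPaCCS". Table 2 repeats it and gives objective 1E the same four exposures. Work package 1 measures socioeconomic position by the IMD, so IMD is itself an exposure and not merely an adjuster.

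The Work package 1 Analysis section fixes how missing outcomes are filled in: "Missing values for key outcomes will be imputed using gender, age, comorbidity, cause of death, IMD and/or study area". The list has no wording such as 'for example' that would leave it open. Age and gender are on it. Ethnicity is not, and 'and/or' allows a model without IMD. The same section lists the study's social determinants with ethnicity among them: "The study will categorise the data into social determinants of health (age, gender, ethnicity, social deprivation), clinical characteristics and elements relating to ACP".

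The next sentence builds each ACP outcome by categorising documented decisions into a binary or ordinal variable for logistic regression. The section also assumes a missing-not-at-random mechanism and plans to compare estimates with and without imputation if imputation is done. It does not define key outcomes. Nothing elsewhere in the protocol adds ethnicity to the outcome imputation.

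**The concern.** An outcome-imputation model that leaves out an exposure of the analysis model draws outcomes that do not depend on that exposure, given the predictors it does use. When observed and imputed records are then analysed together, the adjusted coefficient for that exposure mixes the real association with an imposed null.

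Work package 1 is meant to identify unequal access and to inform training in culturally competent care. With missingness unrelated to the outcome, this error hides ethnic differences, and hides differences by deprivation too if IMD is dropped. It comes from the stated rule and not from the data, and it does not shrink as the registers grow.

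**Working it through.** The protocol states no missingness rate, completion rate or ethnicity effect for these outcomes, so it has no figure of its own to reproduce. The values below are assumptions chosen to show scale.

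**Closed form.** Assumptions:
- 70% have the outcome in the reference group (p0 = 0.70).
- The minority share is 25%.
- The true odds ratio (OR) is 0.60.
- Ethnicity is independent of the listed predictors.
- A fraction m of outcomes is missing, unrelated to outcome or group.

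Steps:
1. Reference odds = 0.70/0.30 = 2.333. Minority odds = 0.60 × 2.333 = 1.400, so p1 = 1.400/2.400 = 0.5833.
2. Without ethnicity, both groups are imputed at the pooled value: 0.75 × 0.70 + 0.25 × 0.5833 = 0.6708.
3. After imputation each group has q = (1 − m) × p + m × 0.6708. The risk difference is therefore (1 − m) times the true one.

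| Imputed share m | Minority q | Reference q | OR | Share of log OR kept |
|---|---|---|---|---|
| 10% | 0.5921 | 0.6971 | 0.63 | 0.90 |
| 20% | 0.6008 | 0.6942 | 0.66 | 0.80 |
| 40% | 0.6183 | 0.6883 | 0.73 | 0.61 |
| 60% | 0.6358 | 0.6825 | 0.81 | 0.41 |

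About a fraction m of the log OR is lost.

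**Simulation.** This allowed ethnicity and IMD to be correlated. It used 15 500 records (the Leeds figure in Table 1), 20 replicates and 5 imputations. Further assumptions were a 30% minority share, a true ethnicity OR of 0.50, a true IMD OR of 0.74 per standard deviation, outcomes missing completely at random, and an ethnicity–IMD correlation of 0, 0.3 or 0.5.

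| Imputation model | Estimate | 10% missing | 30% missing | 50% missing |
|---|---|---|---|---|
| Ethnicity out, IMD in | Ethnicity OR (true 0.50) | 0.54 | 0.61–0.62 | 0.70–0.72 |
| Both out | IMD OR (true 0.74) | about 0.77 | about 0.82 | about 0.87 |
| Both in | Ethnicity OR (true 0.50) | 0.50–0.51 | 0.50–0.51 | 0.50–0.51 |

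- The attenuation of the adjusted ethnicity OR is nearly the same at every correlation. Keeping IMD does not rescue it.
- The crude ethnic gap in the imputed values is about 0 at correlation 0, −0.06 at 0.3 and −0.11 at 0.5. Some ethnic difference does pass through IMD.
- Complete-case ethnicity ORs stay at 0.50–0.51, so under this missingness the stated rule does worse than no imputation.

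**The case against.** The strongest objection is that objective 1D concerns completion of ACP elements. If completion is the outcome, a blank field means not completed, so nothing is missing and nothing is imputed. For objective 1E the outcome is having a record, which is unlikely to be missing. This stands and limits the point to analyses where the outcome is the documented decision and blanks count as missing. The Analysis section permits that reading, because it derives the outcomes from documented decisions immediately after stating the imputation rule.

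A second objection is that the approach is provisional, a full statistical analysis plan is promised, and the comparison with and without imputation would expose the shift. Exposing it is useful, but the comparison neither corrects the estimate nor says which one leads. The predictor sentence is firm, and an analysis plan that followed it would inherit the problem. The point is about what the protocol fixes, not about detail left for later.

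A reader might infer more than the text supports:
- **That imputed outcomes show no ethnic difference at all.** They keep whatever runs through the listed predictors. It is the adjusted association that suffers.
- **That the bias is certainly towards no inequality.** That direction was shown only for missingness unrelated to the outcome. The protocol assumes otherwise.
- **That study area is a constant.** It is true that "The data from each of the three distinct EPaCCS will be analysed separately", but the term is undefined. Table 1 gives 32 commissioning groups in London, and both Bradford and Airedale districts, so an area variable could vary within a register.
- **That the rule contradicts the Missing data considerations section.** There, "Individual-level missing data of the primary outcome variable (place of death) will be excluded from the multivariable analysis". That rule belongs to Work package 2 and the imputation sentence to Work package 1. A conflict arises only if place of death was meant as a key outcome, which is not stated.
- **That cause of death is unusable.** The difficulty is confined to the London records outside the deceased count (140 000 − 100 000 = 40 000). The Leeds and Bradford records are of decedents.

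**Conclusion.** The point holds in a limited form. The stated predictor list omits one objective 1D exposure and makes another optional. Where documented decisions are the outcome and blanks are imputed, the adjusted associations for those exposures are attenuated roughly in proportion to the share imputed.

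The size cannot be settled from the protocol. Under the closed-form assumptions, a true OR of 0.60 moves only to 0.63 at 10% imputed, but to 0.73 at 40%. Under the missing-not-at-random mechanism that the protocol assumes, further bias could add to this attenuation or offset it. Where completion itself or possession of a record is the outcome, this problem should not arise. The wording should be corrected before the analysis because the error bears on a main question of Work package 1 and is easily removed.

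**What to change.** In the Work package 1 Analysis section:
1. Name the outcomes that may be imputed.
2. State that a blank ACP field counts as not completed, and is not imputed, when completion is the outcome.
3. For any outcome that is imputed, require the imputation model to contain every variable of its analysis model: ethnicity, IMD, age, gender and all adjusters. Replace 'and/or' with a fixed list.
4. Use cause of death as a predictor only for records of people recorded as dead.
5. Keep study area where it varies within a register, and say what it denotes.

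The cost is a few sentences. Ethnicity and IMD are already planned as exposures in these regressions, so no new data are needed. In the simulation, including both returned the ethnicity OR to 0.50–0.51 (true 0.50) and the IMD OR to 0.74–0.75 (true 0.74). This removes the bias from the omitted variables. It does not deal with data missing not at random, for which the sensitivity analyses are still needed.
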